### Assessment of RE-AIM

All institutions within the IMPLEMENT network involved in the delivery of qOET are assessed using a dedicated questionnaire (see Supplemental file 3 for full questionnaire). This tool collects relevant data to estimate the impact of the IMPLEMENT project with respect to the primary and secondary outcomes (see add file 2):

The RE-AIM categories of Reach, Effectiveness, Adoption, Implementation and Maintenance.Indicators of qOET to ensure that all conditions for providing a qOET are met by the institution.

Each institution is required to report the number of cancer patients who received qOET during a specified three-month period in the previous year, as well as the overall number of cancer patients with a primary diagnosis over the preceding year. Assuming the overall number of cancer patients remains relatively stable from year to year, we aim to calculate the proportion of cancer patients receiving qOET. We anticipate that this proportion will increase due to the specific IPS interventions.

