**Methods:**

The IMPLEMENT project is designed as an exploratory study with a quasi-experimental design and a mixed-methods approach, combining qualitative and quantitative data collection. Institutions involved in the treatment and/or aftercare of cancer patients will be approached to identify key barriers and facilitators of qOET. Based on these findings, a set of implementation strategies (IPS) will be developed, implemented, and evaluated to facilitate the delivery of qOET for cancer patients. We aim to develop a variety of IPS for different contexts: urban settings (e.g. qualifying local aftercare institutions to provide qOET); rural settings (e.g. a hybrid approach for areas with limited access to local qOET services); adult cancer patients (e.g. focussing on patient education); and children and young cancer patients (e.g. offering consultations with training therapy experts). Additionally, interface management, training concepts, digital support, and economic evaluation will be considered to further promote the wider dissemination of qOET. The impact of the IPS will primarily be measured by the reach of qOET, assessed by comparing the number of cancer patients receiving qOET before and after implementation.

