With respect to the low number of centres offering qOET and high levels of physical inactivity in adult and paediatric cancer patients, the fragmented landscape highlights the urgent need for national efforts to integrate qOET into routine cancer care in Germany [7, 17]. The evidence supporting qOET for cancer patients, combined with the current lack of its implementation in Germany, forms the overarching rationale for the IMPLEMENT project. IMPLEMENT aims to strengthen the implementation of qOET in cancer patients across Germany by identifying and addressing multiple barriers and facilitators. The project aims are structured around the RE-AIM (Reach, Effectiveness, Adoption, Implementation and Maintenance) framework [18]. The primary outcome of IMPLEMENT is to expand the reach of qOET, specifically by increasing the overall number of cancer patients receiving qOET. Additionally, secondary outcomes have been developed in line with the RE-AIM framework (see additional file 2 for the full list). Key secondary outcomes involve:

Increasing the number of cancer patients reporting a significant positive impact of qOET on their daily life (effectiveness).Expanding the number of institutions offering qOET (adoption).Promoting the qOET professional training programme and increase certification by at least 50% of therapists (implementation consistency).Ensuring the sustainability of implementation options to provide qOET provision beyond the three-year project period through the promotion of funding opportunities (maintenance).

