### SP1c: urban areas

The main goal of SP1c is to increase the number of local institutions, particularly physical therapy facilities, capable of providing qOET to cancer patients. In a first step, local physical therapy facilities are identified through personal contacts and/or a web-based search. If available, the facility’s website is reviewed for information regarding services for cancer patients and relevant billing options. Secondly, information materials outlining the benefits of qOET, current training and education options for health care professionals (see SP2), and details about the IMPLEMENT project are sent to the facility by mail and email. With the facility’s consent, IMPLEMENT staff conduct a personal visit to evaluate which qOET requirements, relating to knowledge, equipment, spatial requirements, staff qualification, and financing, are not being met. Finally, facilities receive tailored support to address the identified gaps until all qOET requirements are fulfilled. If staff qualification is identified as a need, therapists are referred to SP2 for appropriate training. Institutions fulfilling all qOET requirements are encouraged to participate in the referral management processes established under SP1e.

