### SP1e: interface management

SP1e activity aims to enhance collaboration across acute care, rehabilitation, and aftercare sectors. Mixed-methods analyses will identify barriers to access and service integration, guiding the development of interface tools and transition protocols to strengthen sectoral links. As all IPS address different stakeholders along the patient journey, the SP1e focuses on interconnecting stakeholders. As part of a digital referral management and reminder system, information about facilities offering qOET is passed on to both doctors in clinics and to practitioners. This enables health personnel to make specific recommendations for cancer patients.

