### Study population

The design of the IMPLEMENT project necessitates data collection involving various cancer patient populations and stakeholders. This includes stakeholders and cancer patients from all IMPLEMENT sites and their networks who may potentially deliver qOET, refer cancer patients to qOET, or provide related advice. This also includes associations, private medical practitioners, and physiotherapy facilities, and cancer patients eligible to participate in qOET (i.e., without contraindications for qOET). Clinics and institutions will provide aggregated information regarding their relevant patient groups.

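### Reach rests on separate aggregate counts from each institution, so a patient treated at two institutions within the window is reported twice, and such repeats may be more common at follow-up than at baseline

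*Protocol article*

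**What the plan says.** The Introduction defines the primary outcome as reach, pursued by "increasing the overall number of cancer patients receiving qOET". The abstract's Methods paragraph gives the comparison: reach is "assessed by comparing the number of cancer patients receiving qOET before and after implementation". Both describe a headcount of people.

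The data source is the institution questionnaire under Assessment of RE-AIM: "Each institution is required to report the number of cancer patients who received qOET during a specified three-month period", taken from the previous year. The institution also reports its patients with a primary diagnosis over a year. From these a proportion is to be calculated, on the assumption that the overall patient number is fairly stable from year to year. The article does not say whether this proportion is pooled or taken per institution. The section Study population describes the level of the data: "Clinics and institutions will provide aggregated information regarding their relevant patient groups".

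Every network institution that delivers qOET reports. Recruitment of collaborating institutions lists hospitals, medical practices, physiotherapy practices and rehabilitation facilities among the network members.

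Two subprojects bear on movement between these institutions. On SP1e: "SP1e activity aims to enhance collaboration across acute care, rehabilitation, and aftercare sectors". Its tools include transition protocols and a digital referral and reminder system. SP1c brings local physiotherapy facilities up to the qOET requirements and then links them to SP1e: "Institutions fulfilling all qOET requirements are encouraged to participate in the referral management processes established under SP1e".

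**The concern.** The outcome counts people, but the data count people per institution. The two agree only if no patient receives qOET at more than one reporting institution within the window. Hospitals, rehabilitation facilities and physiotherapy practices can be successive stops for the same patient, so some overlap is plausible.

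A constant overlap would largely cancel in a before-after ratio. Here the project may change the overlap itself, because it adds qOET providers and works on the transitions between them. Repeat counts may therefore be more frequent at follow-up, an error in the project's favour that the before-after comparison would not reveal. Better continuity for patients already in qOET could be read as more patients reached.

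This has to be settled when the data are collected. Aggregate counts cannot be de-duplicated across institutions by any later analysis.

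**Working it through.** **The plan's own figure.** None is given for reach. The only power statement (300 patients per time point, effect size 0.3, alpha 0.05, power 95%) concerns the patient questionnaire. It reproduces at 0.957 for a two-sided comparison of two independent samples and has no bearing on reach.

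**Step 1: effect of a changing overlap.**
- From the article: one aggregated count per institution over three months, compared before and after.
- Assumed: U = 1,000 distinct patients at both time points, and h = share also counted at a second institution in the same window. The documents give no value for h.
- Formula, if the institution counts are added: total = U × (1 + h).

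| h at baseline | h at follow-up | Totals | Apparent change |
|---|---|---|---|
| 5% | 5% | 1,050 to 1,050 | 0% |
| 5% | 10% | 1,050 to 1,100 | +4.8% |
| 5% | 15% | 1,050 to 1,150 | +9.5% |
| 5% | 25% | 1,050 to 1,250 | +19.0% |
| 5% | 35% | 1,050 to 1,350 | +28.6% |
| 0% | 30% | 1,000 to 1,300 | +30.0% |

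The number of distinct patients is the same in every row.

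**Step 2: how far the three-month window limits this.** Assume a steady flow of 100 new patients per month, k consecutive qOET stops of L months each with no gap, and a common window of W = 3 months.
- Summed count = 100 × k × (L + W). Distinct patients in the window = 100 × (kL + W).
- Two stops: the share counted at both is W / (2L + W), which is 3/5 = 60% at L = 1, 3/9 = 33% at L = 3 and 3/15 = 20% at L = 6.
- Three stops: the share counted at all three is (W − L) / (3L + W), which is 2/6 = 33% at L = 1, 1/9 = 11% at L = 2 and zero from L = 3.
- A gap between stops lowers these shares. With a common window, a gap of three months or more removes the overlap.

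**Step 3: separating repeat counts from longer stays.** If a share q = 20% of one-stop patients gain a second stop, the summed count becomes 100 × (L + W) × 1.2, and distinct patients in the window become 100 × (L + W + 0.2L).

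| L (months) | Summed count | Distinct patients in window |
|---|---|---|
| 1 | 400 to 480 (+20%) | 400 to 420 (+5%) |
| 3 | 600 to 720 (+20%) | 600 to 660 (+10%) |
| 6 | 900 to 1,080 (+20%) | 900 to 1,020 (+13.3%) |

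The rise in distinct patients comes from longer stays and fits the outcome as defined, since these people are receiving qOET in the window. The rest of the 20% is repeat counting. Starts remain at 100 per month throughout.

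**Step 4: the proportion.** If g is the corresponding duplicate share in the denominator, a pooled proportion changes by the factor [(1 + h1)/(1 + h0)] × [(1 + g0)/(1 + g1)]. The bias cancels fully only if g changes by the same factor as h. The overall number has no denominator to offset it.

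**The case against.** Several points on the other side are sound.

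- **Adding up is inferred.** The article never says that institution counts are summed. It says a proportion will be calculated. A proportion taken within each institution is not distorted for that institution by a patient also treated elsewhere, and a pooled one may be partly offset by its denominator. This stands for the proportion. An overall number drawn from per-institution reports, however, has no other evident route than addition.
- **Documents not shown.** The questionnaire (Supplemental file 3) and the outcome list (additional file 2) may hold a counting rule. So it cannot be said that none exists. Still, a rule that each institution applies to its own list cannot remove duplicates between institutions without linkage or a question about earlier qOET.
- **The window.** A reader might infer that a patient passing from acute care through rehabilitation to aftercare is counted at every stop. The article does not support that: only stops that deliver qOET and overlap the window count, and Step 2 shows that three will seldom fit. Two can. The article also does not say that all institutions share one window, and late joiners complete the baseline when they join. Differing windows would widen the overlap.
- **SP1e and SP1c bring real gains.** A reader might infer that whatever SP1e adds to reach is an artefact. That is not supported. Its referral information goes to clinic doctors and practitioners, many of whom may work where no qOET is offered; the Introduction reports that only 22.7% of surveyed cancer centres met the minimum requirements. A patient referred from such a place is counted once and is a genuine gain. The difficulty is that the counts as described cannot tell the two kinds of referral apart.
- **Exploratory study.** True, and it tempers the weight of the point. It does not change what the primary number means.

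**Conclusion.** The point holds in limited form. An overall number of patients built from aggregated three-month counts per institution will include anyone treated at two reporting institutions in the window more than once. The article states no means of removing the repeats, and the project's own activities may make them more frequent at follow-up. Part of a rise in the total may therefore reflect hand-overs.

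The size is unknown. The figures of +4.8% to +30% rest wholly on assumed shares and a fixed number of distinct patients; they show sensitivity and do not estimate the bias. The conclusion assumes that counts are added to give the overall number and that no cross-institution rule sits in the supplements. For the proportion, even the net effect is undetermined until the article says whether it is pooled. This is worth correcting because it touches the primary outcome at little cost. It does not show that a reported rise would be spurious.

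**What to change.** Keep the outcome as patients receiving qOET. Replacing it with first-time starters would change the primary outcome and leave out patients who continue at the same institution.

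1. In the follow-up RE-AIM questionnaire, ask how many of the reported patients had also received qOET at another network institution earlier in the same window. Asking only about earlier treatment means that each repeat is subtracted once.
2. Use one common three-month window for all institutions at each time point where possible, and record the exceptions.
3. Report reach with and without these patients. Baseline was scheduled for November 2023 to February 2024, so it may not be possible to split it. In that case compare the net follow-up count with the unsplit baseline total as a conservative lower bound. With 1,000 distinct patients at both time points and an assumed 5% baseline overlap, this gives 1,000/1,050, or −4.8%, so it errs against the project.
4. Always show reach by sector (acute, rehabilitation, aftercare) beside any total.
5. Report the transferred patients as an outcome of SP1e.
6. If Supplemental file 3 already contains such an item, say so in the text.

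The cost is about one added question on a form that is completed jointly with a researcher. Some institutions will only be able to estimate transfers, and the headline rise may be somewhat smaller.

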## Abstract

**Background:**

Although quality-assured oncological exercise therapy (qOET) has proven effective for cancer patients at any stage of treatment and during aftercare, it is not yet incorporated into standard care in Germany and, to the best of our knowledge, in any other country. A collaboration involving eight German research institutions was initiated to investigate the barriers and facilitators to implementation and promote the wider dissemination of qOET for cancer patients across various settings in Germany.

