## Introduction

In 2020, 231,400 women and 261,800 men in Germany were newly diagnosed with cancer, corresponding to incidence rates of 549 and 638 new cases per 100,000 inhabitants, respectively [1]. The 5-year absolute survival rates were 58% for women and 52% for men. Among children aged under 18 years, 2,250 new cases were reported, with incidence rates of 16.1 for girls and 18.9 for boys per 100,000 children and a 5-year survival rate of approximately 88% [1]. In terms of population burden, cancer is amongst the top five causes of death in high-income countries, including Germany [1, 2]. For Germany, the incidence of cancer is projected to increase by 23% by 2030 due to an ageing population and factors such as environmental and lifestyle changes [1]. Consequently, the prevention and treatment of cancer remains a major challenge for the German healthcare system.

Supplementing standard cancer treatment with exercise therapy has been proven highly effective in improving patient related outcomes. Meta-analyses of individual patient data and systematic reviews demonstrate the beneficial effects of physical exercise on quality of life, clinical outcomes, and physical functioning in cancer patients. These findings support the recommendation of exercise therapy irrespective of cancer type [3, 4]. Moreover, meeting physical activity recommendations is strongly associated with both the prevention and improved survival rates for several cancer types [5]. Considering its impact on treatment-related adverse effects and side effects, such as fatigue, depression, sleep disturbances, and bone health, exercise is recommended across the entire cancer care continuum [6, 7]. It should follow established exercise guidelines proposed for cancer patients [8]. To ensure high-quality and safe exercise therapy for cancer patients, a personalised concept of quality-assured oncological exercise therapy (qOET), based on oncological training therapy (OTT), has been proposed for implementation in Germany [9]. An adapted concept for promoting physical activity and exercise therapy has been established for paediatric cancer patients as well as adolescents and young adults (AYAs) [10] and is outlined in evidence-based guidelines for Germany [11]. A detailed overview of the principles of qOET for adults and paediatric cancer patients is given in supplemental file 1. Briefly, qOET is characterised by all of the following key requirements:

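### The reach proportion sets a three-month count of all qOET recipients against a twelve-month count of patients with a primary diagnosis, so it is not the share of patients reached

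*Protocol article*

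**What the plan says.** The Protocol article, section Assessment of RE-AIM, fixes both parts of the reach figure. Each institution reports the "number of cancer patients who received qOET during a specified three-month period in the previous year" and the "overall number of cancer patients with a primary diagnosis over the preceding year". The text continues: "Assuming the overall number of cancer patients remains relatively stable from year to year", "we aim to calculate the proportion of cancer patients receiving qOET". It expects that proportion to rise because of the implementation strategies. It states no scaling of three months to twelve, no restriction of the numerator to new starters or to patients diagnosed in the same year, and no alignment of the windows.

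The two figures come from a wide range of sites: "All institutions within the IMPLEMENT network involved in the delivery of qOET are assessed using a dedicated questionnaire". The section on recruiting collaborating institutions lists physiotherapy practices and sports, exercise and rehabilitation facilities among the network members. Adding physical therapy facilities is the main goal of subproject SP1c.

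The Abstract and the Introduction word the primary outcome differently, as a before/after comparison of the number of patients receiving qOET.

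**The concern.** A proportion needs a numerator that is a subset of its denominator over the same period. Here the two differ in three ways.

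- **Window.** Three months in the numerator, twelve in the denominator.
- **Population.** The numerator takes anyone in therapy. The Abstract describes qOET as "effective for cancer patients at any stage of treatment and during aftercare", so recipients can have been diagnosed before the denominator year. The denominator is also not limited to patients without contraindications, although the Study population section applies that limit.
- **Institution.** A physiotherapy practice or aftercare facility that makes no primary diagnoses has no natural denominator, yet every institution delivering qOET is asked for both figures.

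The stability assumption concerns how patient numbers change from one year to the next, and so resolves none of these. At stake is what the figure can support. Its level cannot be read as the share of patients reached. It can also move between baseline and follow-up because programmes change in length or the mix of facilities changes, with no change in how many patients are reached.

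**Working it through.** The document gives no numerical target or sample size for reach, so there is no stated figure to reproduce. Its one power statement (300 patients per time point, effect size 0.3, alpha 0.05, power 95%) concerns the patient questionnaire. It reproduces at 95.7% (two-sided, normal approximation) and has no bearing here.

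**Inputs.** From the document: a 3-month numerator window and a 12-month denominator window. Assumed, because the document gives neither: u, the share of a year's new patients who ever start qOET, and D, the programme length in months. For illustration, A = 1,000 new patients a year and u = 30%, with starts spread evenly. The denominator is first read as diagnoses made in the year.

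**Step 1: the numerator.** Starts per month = uA/12 = 0.30 × 1,000/12 = 25. A patient is counted if therapy overlaps the window at any time, so the expected count is (uA/12)(3+D) = 25(3+D).

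**Step 2: the ratio as written.** Dividing by A gives u(3+D)/12.

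| D (months) | Three-month count | Ratio at u = 30% |
|---|---|---|
| 0 | 75 | 7.5% |
| 3 | 150 | 15% |
| 6 | 225 | 22.5% |
| 9 | 300 | 30% |
| 12 | 375 | 37.5% |

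The ratio equals u only when (3+D)/12 = 1, that is at D = 9. It understates uptake for shorter programmes and overstates it for longer ones. A change from D = 3 to D = 6 multiplies it by 9/6 = 1.5 for any u. The count column moves by the same factor, so a three-month before/after count depends on programme length too.

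**Step 3: the other reading of the denominator.** Suppose it means every primary-cancer patient seen in the year, each in care for T months. The denominator becomes (A/12)(12+T) and the ratio u(3+D)/(12+T). The level changes, but the factor from D = 3 to D = 6 is still 1.5 at a given T.

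**Step 4: matched windows.** Starters in three months over new patients in the same three months give (3uA/12)/(3A/12) = u, whatever D is.

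**Step 5: a denominator to avoid.** If the matched denominator counted all patients under treatment in the window, with treatment length T, the ratio would be 3u/(3+T). At u = 30% that is 15% (T = 3), 10% (T = 6) and 6% (T = 12), so length dependence would return. The denominator must be limited to newly diagnosed or newly presenting patients.

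**The case against.** The strongest reply is that the primary comparison is a count, not this ratio. That stands: the Abstract and Introduction both word it so, and no denominator objection touches a count. A reader might infer that the primary outcome as a whole is invalid; the documents do not support that. What remains against the count is its dependence on programme length over a three-month window.

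Second, the factor (3+D)/12 cancels in a relative before/after comparison if programme length, facility mix and calendar window stay constant. That is correct, and none of the strategies is described as lengthening programmes. The document does not state constancy either. Network expansion is a desired consequence of the project, and hybrid rural delivery and links into aftercare could alter both length and mix.

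Third, the questionnaire (Supplemental file 3) is not shown and may define the terms more closely. This limits certainty about item wording. It does not change the two windows that the article itself states.

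Fourth, a reader might infer that the ratio can exceed 100%. Under the reading as diagnoses made in the year it can: with u = 50% and D = 24, 0.50 × 27/12 = 112.5%. If the denominator means all primary-cancer patients seen in the year, this is unlikely. The wording allows both readings, so the point does not rest on it.

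Finally, it is tempting to set the stability assumption against the Introduction's statement that "the incidence of cancer is projected to increase by 23% by 2030". Counted from 2020, 1.23^(1/10) is about 1.021, or roughly 2.1% a year and 4.2% over two years. That is compatible with relative stability and is no contradiction.

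**Conclusion.** The concern holds in limited form. The ratio, as the article defines it, is not the proportion of cancer patients receiving qOET, because windows and populations differ and no scaling is stated. Its level depends on programme length under either reading of the denominator, and it has no clear meaning at facilities that make no primary diagnoses.

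The figures in the table are illustrations. They rest on a steady state, even starts, and assumed values of u and D. A reader might infer that reported reach will be inflated by 50%. The documents do not support that as a forecast; the factor only shows how far the figure would move if programmes went from three to six months with uptake unchanged. The project is exploratory and its primary comparison is worded as a count, so the consequence is a limit on what the reach proportion can be used to claim.

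**What to change.** 1. Keep the before/after count of patients receiving qOET as the primary reach measure, and report beside it the number who started qOET in the window. Starters do not depend on programme length.
2. Calculate a proportion only for diagnosing or treating institutions: starters in the window over patients newly diagnosed or newly presenting at that institution in the same window.
3. Use each wave's own denominator in place of the stability assumption.
4. For all other facilities, report counts only.
5. Where baseline starters or matched denominators cannot be retrieved from records, report the existing ratio as an index, not a proportion, and compare it only within institutions reporting at both waves.

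The cost is a small extra reporting burden and possibly incomplete baseline data. Baseline ran from November 2023 to February 2024 and follow-up is scheduled for November 2025 to February 2026. Baseline figures requested at follow-up would therefore reach back two years or more, and should come from records and not from recall.
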